***Pre- and Post-Test Measures***		
Hauora—tinana/hinengaro	Self-rated health	1
Hauora—tinana/hinengaro	Health related quality of life—physical and mental wellbeing	7
Hauora-wairua	Spiritual wellbeing	1
Hauora-whanaungatanga	Loneliness	4
Hauora-whanaungatanga	Cultural connection	3
Hauora-whanaungatanga	Social support	4
Mana motuhake	Perceived autonomy	1
Mana motuhake	Global life satisfaction	1
Mana motuhake	Sense of purpose	3
Mana motuhake	Historical trauma	4
Demographics	Living situation, relational status, gender, age, iwi (tribe)	5

The participants can complete the questionnaire on their own or via a structured interview administered by a Māori research team member and can have a support person present if desired (data will be collected on questionnaires to assess potential bias). The questionnaire will have both te reo Māori and English language versions. The te reo Māori version will involve a translation and back-translation procedure to ensure equivalence to the English version. The questionnaires will be written with plenty of space and large font to support the reading needs of kaumātua. Focus groups will be conducted at the end of the approach and are able to be held in either English or Te Reo Māori. Consistent with previous research, participants will receive a $50 koha for each data collection point and related events.

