#### Data collection measures/procedures

A common set of quantitative and qualitative measures will address the core themes of hauora and mana motuhake, mostly using scales validated from the previous KMM research [36, 97]. For hauora (hinengaro [mental], tinana [physical], wairua [spiritual], and whanaunga [social]), the following items/scales will be used: self-reported health [98, 99], mental/physical health-related quality of life (HRQOL) [100, 101], spiritual wellbeing [102], loneliness [2, 103], perceived and desired social support [104], and cultural connection [40]. Mana motuhake will be measured via perceived autonomy [105], life satisfaction [106], sense of purpose [107], and historical trauma [65]. See Table 1 for a list of constructs and measures. Qualitative data will be formed from open-ended questions about impressions and impacts of the intervention on the same instrument. The total number of items in the common survey excluding demographics will be 29; this allows approximately 15–20 items related to specific projects without overburdening kaumātua. All measures will be revisited during the co-design process to ensure relevance and appropriateness, particularly using the knowledge and experience of the advisory group members and providers. Up to two focus groups with participants will be hosted at each location, with another provider focus group dedicated to provider-level outcomes relating to specific projects. This mix of quantitative and qualitative data provides a robust data set that supports triangulation of the research findings.

**Table 1 Tab1:** Constructs and Measures Common to both Projects

Construct	Measures	Number of Items

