#### Cultural safety and research ethics

The research team will seek ethics approval through the University of Waikato’s Human Research Ethics Committee for each project separately. Furthermore, the research team will work with the advisory groups to develop a training procedure around data collection (including secure data management procedures) that ensures participant safety. Given the researchers’ previous experience interviewing kaumātua, a culturally appropriate approach for data collection developed in earlier projects [108, 109] may be used including karakia, whakawhanaungatanga, shared kai, kanohi-ki-te-kanohi, koha and whakawhitiwhiti whakaaro (collective debrief).

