**Fig. 2 Fig2:**
[figure not shown]
Planned CONSORT Flow Diagram and Data Collection for Tuakana-Teina Project. Note: Participants not allocated to intervention, lost to follow up and excluded from analysis will be calculated at the conclusion of the intervention

The sample size was determined by a balance of resources and power to determine the optimal design and confirmed with the od.exe software [121]. Twenty tuakana and 120 teina will be recruited in total from the five providers; with all tuakana retained/replaced and 67% of teina retention as occurred in a previous iteration of this model [36] it is expected that at least 20 tuakana and 80 teina will be retained. With the assumption of *p* = .05 and intra-class correlation = .01 (from our previous study) [36], there will be sufficient power (=.80) to identify a medium effect (d = .5) in change over time and a group X time interaction. A medium effect size was chosen given prior research on the impact of elder peer educators on self-rated health and related wellbeing outcomes [122, 123] and our previous research [36].

For specific measures, this project will use a measure of elder abuse adapted from a previous scale [124], housing (two items created for the study; one adapted from the Māori Social Survey) [102], and three items on service use and satisfaction (two created for this study and one from our previous project) [36]. See Additional file 1 for the items created for this study. The project has been prospectively registered with Australia New Zealand Clinical Trial Registry (ACTRN12620000316909); it has also received research ethics approval (HREC2019#81).

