To test the objective, a mixed-model regression analysis will be used where the participant responses over the three time periods are nested within individual teina and within providers (i.e., a three-level model). Mean responses for each of the key outcomes will be used as the dependent variables (e.g., HRQOL, life satisfaction, health service utilisation (depression). The model will include the following independent variables: a) within group responses (i.e., responses for three time periods) for change over time; b) intervention received or not to identify intervention effect; and c) random intercepts to account for different teina baseline scores. Co-variates will include any independent variables that differ between the two approach groups at the baseline period. An intent-to-treat analysis will be used for the primary testing. A dose-response model will be considered including number of interactions between tuakana-teina and a rating of conversational quality between the tuakana-teina. Also, it will be examined whether missing data due to loss to follow up can be multiply imputed via chained equations [125].

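### The support-person rule covers the whole questionnaire without exception, so Project 1's elder-abuse items may be answered in front of a relative or carer who may be responsible

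*Protocol article*

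**What the plan says.** The text after Table 1 in Data collection measures/procedures gives the completion rule: "The participants can complete the questionnaire on their own or via a structured interview administered by a Māori research team member". The same sentence adds that they "can have a support person present if desired (data will be collected on questionnaires to assess potential bias". It does not limit who the support person may be and exempts no items.

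The common survey has 29 items apart from demographics, and on the project-specific items the article says that "this allows approximately 15–20 items related to specific projects without overburdening kaumātua". Under Project 1, the paragraph on specific measures says "this project will use a measure of elder abuse adapted from a previous scale".

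Three other statements bear on the point:
- **Cultural safety and research ethics:** the team will work with the advisory groups to "develop a training procedure around data collection (including secure data management procedures) that ensures participant safety".
- **Project 1, ethics:** "it has also received research ethics approval (HREC2019#81").
- **Data collection measures/procedures:** "All measures will be revisited during the co-design process to ensure relevance and appropriateness".

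**The concern.** Abuse questions differ from the rest of the survey because the answer can depend on who is in the room. If the companion is the relative or carer responsible for mistreatment, a participant may withhold the answer, or may answer truthfully within sight or hearing of that person. The first weakens the measure among the people it is meant to identify. The second is a safety matter.

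There is also a comparative issue. At post-test 1 only the first group of providers has received the approach. If companions are present more often in one group or at one wave, recorded abuse could differ for that reason alone. The rule does not hold the setting constant.

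**Working it through.** No power, alpha or sample-size figure decides this point. The check is mainly a reading of the passages together, followed by an illustration on assumed values.

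**1. Do the abuse items fall under the rule?** The common items in Table 1 sum to 1 + 7 + 1 + 4 + 3 + 4 + 1 + 1 + 3 + 4 = 29, which reproduces the stated total. None is an abuse item, so the abuse measure belongs to the 15–20 project-specific items. The article budgets these alongside the 29 as one burden on the respondent, which supports reading them as one questionnaire under one rule. It mentions no separate instrument or session for them.

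**2. Does anything stated exclude a companion for these items?**

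| Provision | What it does | Does it make the abuse items private? |
|---|---|---|
| Completion alone is offered | Allows privacy | Not required |
| Support person only if desired | Leaves the choice to the participant | Protects least where the companion has influence over that choice |
| Data recorded to assess bias | Allows a later comparison | No; acts after the answer is given |
| Safety training, to be developed | General commitment | Private administration not mentioned |
| Topics under Training for researchers | Ethics, needs of kaumātua, cultural processes | Abuse items and privacy not named |
| Ethics approval for Project 1 | Confirms review | Says nothing about how these items are asked |

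Nothing shown prevents the situation described.

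**3. Can the recorded data repair it?** Only partly. Comparing answers by companion present or absent is possible, but participants choose whether to be accompanied. A difference could reflect non-disclosure or a real difference between those who bring someone and those who do not. The comparison cannot recover an answer that was withheld.

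**4. Illustrative size.** The documents give no prevalence, no accompanied share and no disclosure rate, so all values here are assumptions. Treat the measure as yes/no. Let s be the share of abused participants who answer with a companion present, and r the fraction of abuse reported in that setting. Assume full reporting otherwise. Then

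recorded prevalence ÷ true prevalence = 1 − s(1 − r)

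- s = 0.1, r = 0.5: 1 − 0.1 × 0.5 = 0.95
- s = 0.3, r = 0.5: 1 − 0.3 × 0.5 = 0.85
- s = 0.5, r = 0.2: 1 − 0.5 × 0.8 = 0.60

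If s and r are the same in both groups and at all waves, a true difference in prevalence shrinks by that same factor. If they differ, the error can go either way. With equal true prevalence and factors of 0.95 and 0.85, the apparent ratio is 0.95 ÷ 0.85 = 1.12, or 0.85 ÷ 0.95 = 0.89 with the groups reversed.

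**The case against.** The best defence is that this is a condensed article. How sensitive items are asked, who may act as support person and what follows a disclosure would normally be set out in a full protocol, interviewer manual or ethics file. Measures were also to be revisited in co-design. This stands in part: the absence of a disclosure pathway is not a finding, and none is claimed here. The point concerns a rule that the article does state, for the questionnaire as a whole.

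A reader might go further in several ways that the documents do not support:
- **That the rule does bias the measure and does endanger participants.** This needs an abused participant, accompanied by the person responsible, who does not use the private option. The support person is optional and is not said to be a relative or carer.
- **That recording data on bias is the only safeguard.** The article also promises safety training for data collection and reports ethics approval.
- **That first-group teina would bring their tuakana, distorting the post-test 1 comparison.** Nothing says tuakana may or would act as support persons.
- **That a single under-count, such as 25%, can be stated.** That figure needs an assumed prevalence, accompanied share and non-disclosure rate, none of which is given.
- **That a key outcome is compromised.** Elder abuse is listed as a specific measure. The examples of key outcomes do not name it: "Mean responses for each of the key outcomes will be used as the dependent variables (e.g., HRQOL, life satisfaction, health service utilisation (depression"). That list is only illustrative, so elder abuse may still be analysed, but no stated conclusion is shown to depend on it.

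A further fair objection is that insisting on privacy has its own cost. Answers may be lost from participants whose companion will not leave, and a support option is removed in a design led by kaumātua. This stands, and the fix has to allow for it.

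**Conclusion.** The point holds as a conditional risk created by a stated rule. The completion procedure and the Project 1 measures, taken together, permit elder-abuse items to be answered in front of a person who may be responsible. The stated provisions neither prevent this nor mention private administration. Under-reporting of this one measure is plausible and a participant may be put at risk.

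The size and direction of any bias cannot be derived from the documents. The 0.95 to 0.60 range and the ratios of 1.12 and 0.89 rest wholly on assumed values. The conclusion assumes that the abuse items are part of the questionnaire to which the rule applies, and that no document outside the article already exempts them. It does not extend to HRQOL, life satisfaction or the other common measures.

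**What to change.** Except the elder-abuse items from the support-person option. Put them in a separate section completed privately: self-completed and sealed, or asked by the interviewer with the support person out of the room. Use the same procedure at all three waves and in both groups, and cover it in the data-collection training already promised. Keep the support-person option for every other item.

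Where privacy cannot be arranged, record that as the reason the items are missing and report its frequency by group and wave. This missingness may be related to abuse, so it should not be treated as ignorable or merged with loss to follow-up.

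The change needs a sentence in the procedure, a separate questionnaire section and a line in the training. The planned co-design review of measures is a natural place to agree it with the advisory groups. The downside is some additional missing answers, possibly concentrated in participants who are at risk or who need help to respond. The procedure therefore exchanges some undetected under-reporting for missing data that can at least be seen and counted.

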#### Cultural safety and research ethics

The research team will seek ethics approval through the University of Waikato’s Human Research Ethics Committee for each project separately. Furthermore, the research team will work with the advisory groups to develop a training procedure around data collection (including secure data management procedures) that ensures participant safety. Given the researchers’ previous experience interviewing kaumātua, a culturally appropriate approach for data collection developed in earlier projects [108, 109] may be used including karakia, whakawhanaungatanga, shared kai, kanohi-ki-te-kanohi, koha and whakawhitiwhiti whakaaro (collective debrief).

#### Data analysis

Prior to conducting the primary data analysis, psychometric properties of the scales will be re-affirmed to ensure there are not regional differences. Psychometric properties of specific scales that have not been validated with Māori populations will also be established within the projects. Factorial validity will be assessed with confirmatory factor analysis and reliability established with Cronbach’s alpha. Analysis will be completed with AMOS 26 [110].

Qualitative data will be analysed using thematic analysis [111] following procedures used in previous work with kaumātua. Each analysis will be undertaken by two research team members, with at least one Māori team member [108, 112], whilst it is also likely kaumātua will be included in this phase of analysis. At the very least, themes will be shared with kaumātua and service providers as a validity check to assess if revisions to the analysis are required.

Quantitative data analysis will include several steps. First, statistical assumptions including patterns of missing data will be assessed. Second, descriptive statistics including means, standard deviations, and confidence intervals for continuous data and frequencies for categorical data will be provided. Finally the analysis will involve multilevel analysis of mixed models following procedures to isolate the effect of the intervention across different groups at different times using average treatment effect on the treated [113]. In addition, we will include nesting of repeated measures within individual teina and teina within intervention group. Analysis will be completed with SPSS 26 [114]. Specific models will be identified for the projects.

Finally, estimates of cost effectiveness will be determined using incremental cost effectiveness analysis (ICEA) [115, 116]. ICEA involves estimating the cost per unit improvement in the outcome variable. There are multiple outcome variables in this research programme; however, because it is reasonable to expect that changes in these variables are highly correlated, using 1–2 variables should be sufficient [117] (likely to be HRQOL [hauora] and sense of purpose [mana motuhake] pending advisory group consultation). ICEA involves estimating the ratio of the increase in the outcome variable (as measured by the estimated effect size from the approach trial) to the estimated average cost per participant of the research programme (the incremental cost-effectiveness ratio; ICER). This calculation assumes that the cost of the status quo (no approach) is zero. ICER is a common measure used in the evaluation of the cost-effectiveness of health approaches [118, 119].

Data analysis will be completed for both projects separately; thereafter, results will be compiled into a collective report to compare the analysis by project (including comparisons of impacts on common outcomes), and to disseminate the findings to various stakeholders. This integration will help service providers and other end-users assess whether specific projects meet the needs of kaumātua.

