### Research aims and objectives

The broader objective of this research is to empirically demonstrate that Indigenous cultural revitalisation will increase the wellbeing of Indigenous communities. KMMP is comprised of two interrelated projects that foreground dimensions of wellbeing within a holistic Te Ao Māori (Māori epistemology) view of wellbeing. This view incorporates dynamics of individual perspectives, participation in Māori community, and interconnectedness among spiritual, cultural, whānau (extended family), community, and material wellbeing. Both projects will focus on identified aspects of cultural continuity including te reo, tikanga, mātauranga (cultural knowledge), Māori values, cultural and whānau roles of kaumātua, and intergenerational knowledge exchange. Project 1 involves a tuakana-teina/peer educator model approach focused on increasing service access and utilisation to support kaumātua with the greatest health and social needs through. Project 2’s approach focuses on physical activity and mātauranga exchange (including te reo Māori; Māori language) through intergenerational models of learning. In addition, the research programme involves a network of 11 Māori service providers.

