## Specific research projects

### Project 1 – Tuakana-teina peer education

This project builds on the model from a previous project [36], which resulted in significant gains in social support/connection, life satisfaction/mana motuhake, and HRQOL helping kaumātua prepare for life transitions [36, 37, 94]. While the model was trialled in that project, the current version is a significantly enhanced model with two elements that make it innovative. Firstly, service providers noted the need to test the model with other providers. Secondly, service providers believed that the model could be more effectively applied to kaumātua with greatest needs rather than generally for life transitions, particularly in the context of research showing that Māori are more likely to have unmet needs for primary health care than non-Māori [120]. Through the co-design process the research team will work with each service provider to identify the key health and social issues particular to their community.

Once these are defined and a resource kit is created to guide kaumātua, a small number of kaumātua (*n* = 4) will be purposively selected from each service provider and will take part in a Tuakana Orientation Programme. This programme includes four workshops that offer suggestions for communication skills ground in Te Ao Māori and practice around being a peer educator with specific details identified elsewhere [37]. They will then serve as tuakana (peer educator/supporter) for six teina (recipient of peer education/support) for a period of 6-months. Tuakana will talk with teina up to six times to understand their needs and empower them to gain access to needed health and social services. A community research serves as a coordinator for the project and is a resource for helping tuakana and teina link to specific services. The community researcher also provides a resource booklet of available services in the community that tuakana share with teina during the conversations.

Five providers will participate in this project. We will attempt to randomly select teina using a list of registered kaumatua from each provider (*n* = 24 per provider) and exclude participants with advance dementia or cognitive impairment and any other health conditions the provider feel would negative impact participants. Figure 2 provides a flow diagram of proposed recruitment and data collection procedures.

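### The cost-effectiveness ratio is defined in two reciprocal ways, and its cost is that of the research programme although effects are estimated project by project

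*Protocol article*

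**What the plan says.** All the defining text is in one paragraph of the protocol article, Methods and design, Data analysis.

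- Purpose: "ICEA involves estimating the cost per unit improvement in the outcome variable".
- Definition, two sentences later: "ICEA involves estimating the ratio of the increase in the outcome variable", with the increase measured by the trial's estimated effect size and related "to the estimated average cost per participant of the research programme". The abbreviation ICER is attached to this ratio.
- Comparator: "This calculation assumes that the cost of the status quo (no approach) is zero".

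The next paragraph of that section says that the two projects will be analysed separately and then compared in a collective report. The Background section uses the term research programme for KMMP as a whole, and Research aims and objectives says that KMMP comprises both projects.

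On service use, Research aims and objectives describes Project 1 as "focused on increasing service access and utilisation to support kaumātua with the greatest health and social needs". The Project 1 section says that tuakana talk with teina to "empower them to gain access to needed health and social services". On research payments, Data collection measures/procedures says that "participants will receive a $50 koha for each data collection point and related events".

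**The concern.** A named, prespecified measure has two definitions that cannot both be the ICER. Cost over effect improves as it falls; effect over cost improves as it rises. The paragraph also calls the ICER a common measure in evaluating health approaches, so readers will bring its usual direction to whatever number appears under that label.

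The cost term has a separate problem. The sentence takes the effect from the trial of an approach and the cost from the research programme. If that term keeps its meaning from the rest of the article, a programme-wide cost is set against a project-specific effect, and costs of doing research may be mixed with costs of delivering the approach.

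The abstract and the Discussion anticipate that both approaches will be cost effective. The Discussion intends to use them in advocacy with policy-makers if they prove effective, and the collective report will compare the projects. A ratio of unclear direction and unclear cost would serve neither use.

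**Working it through.** The article gives no ICER, cost total or threshold, so there is no figure to reproduce. The check is algebraic, followed by an illustration.

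**Definitions.** Let E be the gain in outcome and C the average cost per participant.

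- Purpose sentence: C / E.
- Sentence labelled ICER: E / C, which is 1 / (C / E).
- Usual incremental form: (C1 − C0) / (E1 − E0). With C0 = 0 this becomes C1 / E, which agrees with the purpose sentence and not with the labelled one.

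**Illustration.** E = 0.5 is the Project 1 planning effect and E = 0.3 the Project 2 planning effect for the group-by-time interaction, both in standard-deviation units. The article gives no cost per participant, so C is assumed over a range.

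| Assumed C | E / C at 0.5 | C / E at 0.5 | E / C at 0.3 | C / E at 0.3 |
|---|---|---|---|---|
| $250 | 0.002 | $500 | 0.0012 | $833 |
| $500 | 0.001 | $1,000 | 0.0006 | $1,667 |
| $1,000 | 0.0005 | $2,000 | 0.0003 | $3,333 |
| $2,000 | 0.00025 | $4,000 | 0.00015 | $6,667 |

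At any fixed cost, moving from 0.3 to 0.5 raises E / C and lowers C / E.

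**Cost term.** The only dollar amount in the article is the $50 koha. Over the three data collection points (pre-test, post-test 1, post-test 2) it comes to 3 × $50 = $150 for a participant who completes all three, before any related events. If it were counted as cost, it would add 150 / 0.5 = $300 per unit at E = 0.5, or 150 / 0.3 = $500 at E = 0.3. The article does not say that it is counted.

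**Zero comparator.** Write D for delivery cost, and S1 and S0 for service cost with and without the approach. The full increment is D + S1 − S0.

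- If only delivery is costed, the approach costs D, no approach costs 0, and the ratio is D / E. Zero is then coherent.
- Setting C0 = 0 does not by itself remove induced service cost. That cost is absent because nothing but programme cost is counted on the approach side.
- For Project 1 at E = 0.5 and an assumed D of $500, the delivery-only ratio is $1,000. An assumed S1 − S0 of −$200, +$200 or +$500 gives (500 − 200) / 0.5 = $600, (500 + 200) / 0.5 = $1,400 or (500 + 500) / 0.5 = $2,000. Each $100 moves the ratio by $200 per unit, in either direction.

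**The case against.** The best defence is that this is a slip of wording. The conventional purpose is stated first, the ICER is called a common measure, and a health economist would compute cost over effect regardless. No reported number is wrong, and the effectiveness models for both projects do not use the ratio. The paragraph also glosses the status quo as no approach, which suggests that the cost of the approach was meant. All of this limits the seriousness of the point. It does not reconcile the two definitions, and it does not tell an analyst which cost to collect.

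Two stronger readings are tempting, and the article supports neither.

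- A reader might infer that research costs such as the koha will be counted. The literal wording allows it, but no sentence says so.
- A reader might infer that the zero comparator hides induced service cost and so flatters the ratio. Zero is openly declared and is coherent if only delivery is costed, and a choice of costing perspective is commonly left to a fuller plan. The issue concerns Project 1 only, since Project 2 is not described as raising service use. The net direction is unknown: more use adds cost, and averted care removes it.

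Nor can it be assumed that service use could be priced. Project 1 has three items on service use and satisfaction, and nothing shown establishes that they record countable contacts.

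**Conclusion.** The point holds on two counts. First, the paragraph defines its measure as cost over effect and then labels effect over cost the ICER; this follows from the text alone and needs no assumption. Second, the cost is fixed badly: taken literally, it is the cost of KMMP as a whole, which does not match effects estimated by project and can include research-only items. This count rests on the term having the meaning it has elsewhere in the article. Loose wording is possible, and it would call for the same correction.

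The zero status-quo cost is not an error under a delivery-only perspective; that perspective simply needs to be stated. No bias of known size or direction can be claimed from the omission of service costs. Every dollar figure above except the $50 koha and its $150 total is illustrative. The cost-effectiveness analysis stands apart from the outcome models, so conclusions on effectiveness are unaffected. This is a necessary correction of a definition, and a small one.

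**What to change.** 1. Replace the second definition so that the paragraph has one: ICER = (mean cost with the approach − mean cost without) / (mean outcome with − mean outcome without), computed for each project, with lower values better when both differences are positive.
2. Define cost as the delivery cost per participant of that project's approach, excluding data-collection and other research costs. For Project 1, delivery would cover the tuakana orientation, coordination and resource materials. The community researcher both coordinates delivery and supports the project's administration, so state how that time is divided.
3. Say that the zero status-quo cost follows from a delivery-only perspective.
4. Optionally, for Project 1, add a sensitivity analysis that includes the between-group difference in service cost, if the collected items allow service use to be counted and priced. Do not presume its direction.

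Items 1 and 3 are changes of wording only. Item 2 needs delivery and research spending to be recorded separately by project, which is easiest if arranged from the start. Item 4 requires unit costs from an outside source, may be coarse with so few items, and could move the ratio either way.
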